### Sample size

Given the exploratory and observational design of this study, no formal confirmatory sample size calculation was performed.

Reported SSI rates after elective open vascular groin procedures range between approximately 5% and 30%, depending on patient risk profile, procedural complexity, and implantation of prosthetic material [9–11]. Based on these rates, an average SSI incidence of approximately 17.5% was assumed for the standard treatment cohort. As data regarding HOCl irrigation in vascular surgery are currently lacking, the anticipated treatment effect was extrapolated from antiseptic irrigation studies in other surgical settings, suggesting a clinically plausible relative SSI reduction of approximately 50%, corresponding to an expected SSI rate of 8.75% in the HOCl cohort [40, 41].

Based on the expected institutional case volume, approximately 160 procedures (80 retrospective and 80 prospective cases) are anticipated during the predefined observation periods. Using a two-sided Fisher’s exact test with an α level of 0.05, this sample size would correspond to an estimated statistical power of approximately 29.9% for detecting the assumed effect size. Accordingly, the present study is not powered for definitive efficacy conclusions but is intended to allow exploratory estimation of potential effect sizes and clinically relevant trends associated with HOCl-based irrigation under real-world conditions, as well as to generate data for the design and formal sample size calculation of future randomized controlled trials.

### Data management

Study data will be recorded using a Microsoft Excel file and stored on an access-restricted folder on a network drive of the Heidelberg University Hospital, which is not accessible from the internet. Data collection will be performed exclusively within the institutional IT infrastructure.

All data will be pseudonymized at the time of extraction from the electronic medical records. The pseudonymization key will be stored separately and accessible only to authorized study personnel. For statistical analysis and dissemination of results, datasets will be fully anonymized to ensure confidentiality and data security.

### Statistical analysis

The unit of analysis in this study is the index surgical procedure. Each elective open vascular groin operation with arterial exposure constitutes one analytical case. In patients undergoing more than one elective open vascular groin procedure during the study period, each procedure is considered a separate case if it represents an independent, planned surgical intervention. Bilateral elective groin operations are analysed as two distinct cases, as each groin represents a separate surgical site with an independent risk profile for surgical site infection and wound-related complications. Reinterventions, revisions, or reoperations performed because of postoperative complications, including surgical site infection, haematoma, lymphatic fistula, bleeding, or graft-related complications, are not considered new cases but are recorded as postoperative outcomes of the corresponding index procedure.

Continuous variables will be summarized as means with standard deviations or as medians with interquartile ranges, depending on their distribution. Group comparisons will be performed using Student’s t-test or appropriate non-parametric tests. Categorical variables will be reported as absolute counts and percentages and compared using the chi-square test or Fisher’s exact test, as appropriate.

The primary analysis will explore the association between intraoperative HOCl–based wound irrigation and the occurrence of SSI using multivariable logistic regression models. A predefined set of clinically relevant covariates will be included in multivariable models to reduce data-driven selection and temporal bias. These covariates include age, sex, Charlson-Index, ASA physical status, wound contamination class, type of vascular procedure, implantation of alloplastic material, diabetes mellitus, smoking status, body mass index, and duration of surgery. Covariate selection is based on established risk factors for SSI in vascular surgery and on variables expected to differ between sequential cohorts.

Effect estimates will be reported as odds ratios with corresponding 95% confidence intervals. All statistical analyses will be exploratory in nature, and p-values will be interpreted descriptively.

Predefined subgroup and sensitivity analyses, for example stratified by procedure type or wound contamination class, will be conducted to assess the robustness of the findings and to explore potential effect modification. Given the exploratory nature of the study and the anticipated number of outcome events, multivariable analyses will be restricted to a limited number of clinically relevant covariates to avoid model overfitting. Variable selection is therefore predefined and hypothesis-driven rather than data-driven.

As the study uses a sequential retrospective and prospective cohort design, temporal confounding cannot be fully excluded. To improve comparability between cohorts, sensitivity analyses using propensity score-based adjustment methods, including propensity score matching or inverse probability weighting, may additionally be performed depending on event numbers and covariate balance.

The extent and pattern of missing data will be reported for all variables. Complete-case analyses will be performed if missingness for key variables is low (< 5%). If missingness exceeds this threshold and is considered plausibly at random, multiple imputation using chained equations may be applied in sensitivity analyses. Variables with extensive missingness or limited clinical relevance may be excluded from multivariable analyses.

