Details on perioperative antibiotic prophylaxis will be recorded, including the administered agent, timing, redosing, and duration in accordance with institutional standards.

Infection-related outcomes will focus on the occurrence and classification of SSI according to CDC criteria [39], based on clinical and microbiological findings documented during index hospital stay. SSI will be categorized as follows:

Superficial incisional SSI: Infection involving only the skin or subcutaneous tissue of the incision, meeting at least one of the CDC-defined criteria.Deep incisional SSI: Infection involving the deep soft tissues (e.g. fascia or muscle layers) of the surgical site, fulfilling CDC criteria.Organ/space SSI: Infection involving any anatomical structure other than the incision that was opened or manipulated during the surgical procedure, fulfilling CDC criteria.

Postoperative complications will include lymphatic fistula, haematoma, seroma, wound dehiscence, postoperative bleeding, graft-related complications, thrombotic or embolic events, myocardial infarction, stroke, pneumonia, pulmonary embolism, urinary tract infection, and need for surgical or radiological reintervention. All complications will be graded according to the Clavien–Dindo classification, and the Comprehensive Complications Index (CCI) will be calculated for each patient.

Postoperative management parameters will include length of intensive care unit stay, need for reoperation or radiological intervention, duration of antibiotic therapy, and total length of hospital stay. Postoperative laboratory monitoring will include routine infection markers as documented during the inpatient period. Follow-up data will be collected for up to six weeks postoperatively as part of routine vascular surgical aftercare.

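### Bilateral groins are analysed as two independent cases: a small understatement of error for SSI, and duplicate records for patient-level outcomes if the unit rule is applied as written

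*Protocol article*

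**What the plan says.** The Statistical analysis section of the protocol article opens with a rule that has no exception by outcome: "The unit of analysis in this study is the index surgical procedure". For patients operated on more than once, "each procedure is considered a separate case if it represents an independent, planned surgical intervention". For two-sided surgery, "Bilateral elective groin operations are analysed as two distinct cases, as each groin represents a separate surgical site with an independent risk profile". That last sentence goes on to tie the risk profile to infection of the site and wound complications.

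The methods follow in the same section. For continuous variables, "Group comparisons will be performed using Student’s t-test or appropriate non-parametric tests". Categorical variables are "compared using the chi-square test or Fisher’s exact test, as appropriate". The primary analysis relates irrigation to "the occurrence of SSI using multivariable logistic regression models". The adjustment set begins: "These covariates include age, sex, Charlson-Index, ASA physical status, wound contamination class, type of vascular procedure". It continues with alloplastic material, diabetes, smoking, body mass index and duration of surgery.

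The Data collection section uses another level for one outcome: the "Comprehensive Complications Index (CCI) will be calculated for each patient".

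The sensitivity analyses (subgroups, propensity scores, imputation) do not deal with correlation within patients, and Study limitations does not mention it.

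**The concern.** Two groins operated on together belong to the same person, and usually to the same session and the same prophylaxis. If their infection risks are positively correlated, 80 procedures carry less information than 80 independent observations. Methods that assume independence then give intervals that are too narrow.

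The second part concerns outcomes that do not belong to a groin at all. Hospital and ICU stay, in-hospital death, 30-day readmission, systemic complications and antibiotic duration have one value per patient admission. The rationale given for splitting bilateral cases does not reach them, but the unit rule does. Applied literally, one death or one long stay fills two rows. This gives the patient double weight in means, medians and percentages, and makes the standard error too small. The secondary hypothesis rests on stay, antibiotic exposure and the Comprehensive Complication Index, so it is directly affected.

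Because the article gives independence as its reason, this is a stated choice and not a detail left to an analysis plan.

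**Working it through.** **1. The rationale against the plan's own covariates.** The primary model lists eleven: age, sex, Charlson index, ASA, wound contamination class, procedure type, alloplastic material, diabetes, smoking, body mass index and duration of surgery. Seven of them (age, sex, Charlson index, ASA, diabetes, smoking, body mass index) are patient characteristics, identical for two groins operated on together. The plan describes its choice as based on established SSI risk factors and on variables expected to differ between the cohorts. Sites that share seven such factors do not have independent risk.

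**2. The plan's own figure.** Inputs from Sample size: 80 procedures per cohort, SSI 17.5% against 8.75%, two-sided Fisher's exact test, alpha 0.05. Enumerating both binomial distributions gives a power of 29.89%, so the stated 29.9% is reproduced. It treats the 160 procedures as independent.

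**3. Formulas.** Let s be the share of procedures that come in pairs from one patient within one cohort, and ICC the within-patient correlation.

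- Design effect: DE = 1 + s × ICC
- Effective n per cohort: 80 / DE
- Understatement of the standard error: 1 − 1/√DE
- Actual error of a nominal 5% Wald test: 2 × [1 − Φ(1.96/√DE)]

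The article gives neither s nor ICC. Both are assumptions.

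**4. SSI and wound outcomes, s = 10-30%, ICC = 0.2-0.4.**

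| | Low end | High end |
|---|---|---|
| DE | 1 + 0.1 × 0.2 = 1.02 | 1 + 0.3 × 0.4 = 1.12 |
| Effective n per cohort | 80/1.02 = 78.4 | 80/1.12 = 71.4 |
| SE understated by | 1.0% | 5.5% |
| Actual error, nominal 5% Wald test | 5.2% | 6.4% |
| Fisher power at the effective n | 29.0% | 26.2% |

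**5. Patient-level outcomes, both groins in one admission.** Both rows carry the same value, so ICC = 1 and DE = 1 + s. With share s, 80 procedures come from 80 × (1 − s) + 80 × s/2 patients.

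| s | Patients per 80 procedures | DE | Effective n | SE understated by | Actual error, nominal 5% Wald test |
|---|---|---|---|---|---|
| 10% | 76 | 1.10 | 72.7 | 4.7% | 6.2% |
| 20% | 72 | 1.20 | 66.7 | 8.7% | 7.4% |
| 30% | 68 | 1.30 | 61.5 | 12.3% | 8.6% |

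At s = 5% the effect is smaller: DE = 1.05 and an actual error of about 5.6% with ICC = 1; DE = 1.01 with ICC = 0.2.

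**6. The Comprehensive Complication Index.** Data collection calculates it per patient; Statistical analysis sets the procedure as unit. Nothing says whether a bilateral patient contributes one value or two. The level is unreconciled, and no arithmetic can settle it.

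**The case against.** The best defence is that double counting is nowhere stated. The bilateral rule is justified only for infection and wound outcomes, and the per-patient complication index could show that patient-level outcomes are meant to stay at patient level. This stands in part. A reader might infer that every patient-level outcome, the complication index included, is certain to be counted twice. The article does not support that. Duplication is what the unqualified unit rule implies for two groins in one admission; staged operations in separate admissions have their own stay and readmission window.

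A reader might also infer that the primary analysis is seriously affected. The figures do not show that. All seven shared characteristics are in the model, so only residual correlation matters there, and the assumed ICC may be too high. The error rates above are for Wald-type tests. Fisher's test at 80 per cohort is conservative (an actual error of 3.1% at a common rate of 17.5%), so they do not carry over to it.

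Two further inferences fail. Patients operated on before and after the standard change enter both cohorts, but positive correlation between cohorts reduces the variance of the difference; ignoring it does not narrow the interval. And if the bilateral share differs between periods, bilateral surgery would confound stay and morbidity even with one record per patient.

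Finally, cluster-robust variance is compatible with the wording on logistic regression and is often left to an analysis plan, and p-values are to be read descriptively. Both points lower the severity. They do not remove the fault: the article asserts independence as its reason, and it promises 95% confidence intervals and effect estimates for planning later trials.

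**Conclusion.** The concern holds at moderate severity. The independence rationale conflicts with the plan's own covariate list, and the unit rule is too broad for outcomes that belong to the patient.

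For SSI and wound outcomes the consequence is probably small: standard errors understated by about 1-5.5%. For patient-level outcomes of bilateral patients in one admission, following the rule as written understates standard errors by about 5-12% and gives those patients double weight. For the Comprehensive Complication Index the finding is an unreconciled contradiction between two sections, not proven duplication.

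These sizes assume that 10-30% of procedures are in bilateral pairs, that each pair lies within one cohort and, for SSI, that the ICC is 0.2-0.4. With few bilateral cases the effect would be close to nil. The study declares itself exploratory and underpowered, so nothing is decided at the 5% threshold, but its intervals and rates should still be right.

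**What to change.** - Keep the groin as unit for SSI and local wound outcomes, with inference clustered on the patient (for example cluster-robust or GEE standard errors).
- Analyse stay, ICU stay, mortality, readmission, systemic complications, antibiotic duration and the Comprehensive Complication Index once per patient admission, and bring Data collection and Statistical analysis into line on this.
- Add a sensitivity analysis with one procedure per patient.
- Report the number of patients beside the number of procedures, by cohort.
- Remove the claim that the two groins have independent risk.
- Keep a non-identifying patient code in the analysis dataset. Data management says that this dataset will be fully anonymized, and without such a code the clustering could not be recovered.

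The cost is a rewritten paragraph, one software option and one extra data column. Intervals become slightly wider. For patient-level outcomes with an unchanged standard deviation, going from 80 rows to 76 or 68 patients widens them by √(80/76) − 1 = 2.6% to √(80/68) − 1 = 8.5%. Data acquisition is ongoing, so the change can still be made before analysis.

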**Methods:**

Hypoclates:vascular is a single-centre, ambispective cohort study conducted at Heidelberg University Hospital. Adult patients undergoing elective open vascular groin surgery with arterial exposure are included. A departmental standard change introduced intraoperative wound irrigation with at least 250 ml hypochlorous acid–containing Granudacyn^®^ prior to wound closure, with additional irrigation of alloplastic material where applicable. Patients treated before this change form a retrospective control cohort without antiseptic lavage, while those treated thereafter constitute the prospective cohort. The primary outcome is the incidence of surgical site infections classified according to Centers for Disease Control and Prevention criteria. Secondary outcomes include postoperative morbidity, wound-related complications, antibiotic use, length of hospital stay, and overall morbidity assessed by the Comprehensive Complication Index. Multivariable logistic regression will be used to explore associations between hypochlorous acid-based irrigation and infectious outcomes.

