### Outcomes and hypotheses

Our primary hypothesis states that a standardized intraoperative wound irrigation with HOCl–containing Granudacyn^®^ is associated with a lower incidence of early SSI compared with the previous standard of care without antiseptic lavage.

In accordance, the primary outcome is the incidence of early SSI. The primary endpoint focuses on SSI identified up to hospital discharge, but no later than postoperative day 10 ± 2 days (POD10 ± 2). This restriction was chosen to ensure a robust and uniformly assessable endpoint based on routinely documented inpatient care and to minimize bias related to incomplete capture of post-discharge infections in routine clinical practice.

Importantly, patients undergoing elective vascular groin surgery at our institution routinely receive postoperative follow-up six weeks after surgery as part of standard vascular surgical aftercare, including clinical wound assessment. However, this follow-up does not constitute a study-specific active SSI surveillance programme. Therefore, SSI diagnosed after hospital discharge or beyond POD10 ± 2 during routine follow-up will additionally be captured and reported descriptively in accordance with CDC definitions where documented but will not contribute to the primary endpoint.

The secondary hypothesis is that intraoperative HOCl-based wound irrigation is associated with reduced postoperative morbidity, reflected by shorter hospital stay, reduced antibiotic exposure, and a lower CCI following elective open vascular groin surgery.

Secondary outcomes therefore include postoperative morbidity and clinical course parameters, comprising length of intensive care unit and total hospital stay, duration and type of postoperative antibiotic therapy, wound-related complications (e.g. lymphatic fistula, haematoma, seroma), graft-related or vascular complications, need for surgical or radiological reintervention, and 30-day readmission rates. Overall postoperative morbidity will be quantified using the CCI. All outcomes are detailed in Table 2.

**Table 2 Tab2:** Major outcomes of HYPOCLATES:VASCULAR

Primary outcome	▪ Surgical site infections (SSI), including superficial incisional, deep incisional, and organ/space infections

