### Study limitations

Several limitations should be considered when interpreting the findings of this study. First, the sequential ambispective cohort design is susceptible to temporal confounding and residual bias despite planned statistical adjustment.

Second, although patients routinely undergo postoperative follow-up approximately six weeks after surgery as part of standard vascular surgical aftercare, the primary endpoint focuses on SSI detected during the index hospital stay and within POD10±2. As routine follow-up does not constitute a study-specific active surveillance programme, delayed postoperative infections occurring after discharge may still be incompletely captured and therefore underrepresented in the primary analysis.

Third, as a single-center observational study, external validity and generalizability may be limited. Accordingly, the findings of this study should be interpreted as exploratory and hypothesis-generating rather than confirmatory evidence of causal efficacy. Nevertheless, the pragmatic real-world design may provide clinically relevant exploratory data to inform future randomized controlled trials.

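### The secondary hypothesis on stay, antibiotic exposure and CCI has no committed adjusted comparison, although the cohorts are sequential and case mix may shift between them

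*Protocol article*

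**What the plan says.** Outcomes and hypotheses states a directional secondary hypothesis of reduced postoperative morbidity, "reflected by shorter hospital stay, reduced antibiotic exposure, and a lower CCI".

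The Statistical analysis section sets out the comparisons in general terms, without naming outcomes. For continuous variables: "Group comparisons will be performed using Student’s t-test or appropriate non-parametric tests". Categorical variables are to be "compared using the chi-square test or Fisher’s exact test, as appropriate". The section then turns to adjustment. The primary analysis concerns the association of irrigation with "the occurrence of SSI using multivariable logistic regression models", uses eleven listed covariates and reports odds ratios. The abstract describes the scope in similar terms: "Multivariable logistic regression will be used to explore associations between hypochlorous acid-based irrigation and infectious outcomes".

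The same section bases covariate choice partly on established SSI risk factors and partly on an expectation that some variables differ between the sequential cohorts. It adds stratified sensitivity analyses, with procedure type and contamination class as examples. It also allows propensity-score matching or inverse probability weighting, as an option that depends on event numbers and covariate balance. Neither addition names an outcome. Study limitations concedes that "the sequential ambispective cohort design is susceptible to temporal confounding and residual bias despite planned statistical adjustment".

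**The concern.** With a before/after comparison, an unadjusted difference between cohorts mixes any effect of the lavage with any change in who was operated on and how. The protocol accepts this for SSI and adjusts for it. For the three secondary-hypothesis outcomes it fixes no adjusted analysis. Hospital stay, antibiotic duration and CCI are not binary, so neither the planned logistic model nor an odds ratio of that kind fits them as they stand.

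Several listed covariates (procedure type, alloplastic material, ASA class, Charlson-Index) plausibly drive stay and CCI as well as infection. If their distribution moves between the two half-years, the secondary estimates move too, in either direction. The Sample size section gives estimation of effect sizes for later trials as the study's purpose, so a biased estimate matters even where no formal test is claimed.

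**Working it through.** **What is committed, outcome by outcome**

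| Outcome | Committed comparison | Committed adjustment |
|---|---|---|
| SSI (primary) | Multivariable logistic regression | Yes, eleven covariates |
| Hospital stay | t-test or non-parametric test | None |
| Antibiotic duration | t-test or non-parametric test | None |
| CCI | t-test or non-parametric test | None |

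**The plan's own figure.** The only power figure concerns SSI: 29.9% for a two-sided Fisher's exact test, 80 against 80, 17.5% against 8.75%. Exact enumeration gives 29.89%, so it reproduces. The protocol gives no SD, expected difference or power for the secondary outcomes, so what follows is an illustration.

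**Inputs**
- 80 cases per cohort: Sample size section.
- SD of hospital stay 6 days: assumed.
- One procedure type with a stay 3 to 5 days longer: assumed.
- Systematic shift of 10 or 20 percentage points in its share between cohorts: assumed.
- True effect of irrigation: zero.

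**Formulas**
- SE of the difference = SD × √(2/n) = 6 × √(2/80) = 0.95 day.
- Bias b = shift in share × difference in stay.
- Probability of p < 0.05 = Φ(−1.96 + b/SE) + Φ(−1.96 − b/SE).

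**Results**

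| Shift in share | Extra stay | Bias b | False-positive rate |
|---|---|---|---|
| 10 points | 3 days | 0.3 day | 6.2% |
| 10 points | 5 days | 0.5 day | 8.2% |
| 20 points | 3 days | 0.6 day | 9.7% |
| 20 points | 5 days | 1.0 day | 18.4% |

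**Cross-check in SD units.** With 80 per cohort and no true effect, a total case-mix shift of 0.1 SD gives 9.7%, 0.2 SD gives 24.4% and 0.3 SD gives 47.5%. A bias of 0.6 day is 0.6/6 = 0.1 SD, which agrees with the third row above. Larger totals would need several prognostic factors moving in the same direction, or one strong factor moving a long way.

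**Room for adjustment.** The SSI model expects 80 × 0.175 + 80 × 0.0875 = 14 + 7 = 21 events, hence the protocol's caution about overfitting. Stay and CCI would draw on about 160 procedures (fewer if reduced to patients or admissions), so the event count is not the constraint there.

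**Unit of analysis.** Data collection has the CCI calculated for each patient. Statistical analysis counts a bilateral operation as two cases. One patient's CCI and one hospital stay can therefore enter the comparison twice.

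**The case against.** The sentence on t-tests is generic. It sits in a descriptive paragraph, covers baseline variables too, and never says that the secondary hypothesis will be judged by it. An article may leave secondary models to a fuller document. The stratified sensitivity analyses are to be done and mention procedure type, the very confounder in the illustration. The propensity methods are aimed at comparability between cohorts and do not exclude continuous outcomes. Type of antibiotic therapy is categorical and could enter a logistic model. The protocol reads p-values descriptively, calls its findings hypothesis-generating, and says that other perioperative management stays unchanged.

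Much of this limits the point. A reader might infer that these outcomes can only ever be analysed unadjusted. The text does not support that, because optional propensity and stratified analyses exist. A reader might also infer that any case-mix shift will pass for an HOCl effect. That is too strong as well: only shifts in factors that affect these outcomes cause bias, small ones matter little, and the protocol warns about temporal confounding. Chance imbalance is no argument either, since the nominal 5% already allows for it.

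The core stands. The article does state comparisons for continuous variables and does tie its adjusted model to SSI, so the point does not rest on silence alone. The propensity option is not a commitment, and its dependence on event numbers suits SSI rather than stay or CCI. Stratifying about 160 cases does not give a single adjusted estimate. Unchanged perioperative care does not hold the patient mix constant. Reading p-values descriptively does not remove bias from the estimates.

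**Conclusion.** The point holds in a limited form. For hospital stay, antibiotic duration and CCI, the only committed comparison is unadjusted, in a design where the protocol itself anticipates differences between cohorts. A systematic shift in prognostic case mix would bias these estimates. In the illustration the bias is 0.3 to 0.5 day for a 10-point shift (about 6 to 8% false positives) and 0.6 to 1.0 day for a 20-point shift (about 10 to 18%).

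These sizes rest entirely on the assumed SD, stay difference and shift; only the 80 per cohort comes from the protocol. They show that the effect can run from negligible to material, not that a shift has occurred. The exploratory status lowers the stakes but does not remove the problem, because estimation is the declared aim. The change is worth making before the outcome analysis.

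**What to change.** - For hospital stay, antibiotic duration and CCI, state a covariate-adjusted comparison as the analysis of the secondary hypothesis. Use the covariates already predefined, or commit to propensity-score weighting for these outcomes.
- Name a model and an effect measure with a 95% confidence interval suited to each outcome. The choice of model is the study team's; a log-linear model for stay and antibiotic days and a proportional-odds model for CCI are possibilities.
- Use one record per patient or admission for these outcomes, or patient-clustered standard errors.
- Keep the t-tests and rank tests as description only.

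The cost is a few lines of text, a little more programming and some dependence on model assumptions. Adjustment may narrow or widen the confidence intervals, depending on how far the covariates explain the outcome and how strongly they are related to cohort. It does not remove confounding by unmeasured factors. The covariates are already on the data collection list, so no new data are needed.

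### The primary logistic model spends at least 12 parameters on about 21 expected events, so predefining the covariates does not deliver the protection against overfitting that the plan intends

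*Protocol article*

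**What the plan says.** All references are to the protocol article.

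- **Statistical analysis, model.** The primary analysis is multivariable logistic regression of surgical site infection (SSI) on HOCl irrigation. A fixed set of covariates is to be entered: "These covariates include age, sex, Charlson-Index, ASA physical status, wound contamination class, type of vascular procedure, implantation of alloplastic material, diabetes mellitus, smoking status", and then body mass index and duration of surgery. That makes 11. No penalised estimator is named.
- **Statistical analysis, safeguard.** In view of the expected event count, "multivariable analyses will be restricted to a limited number of clinically relevant covariates to avoid model overfitting". The next sentence presents the advance choice of variables as the way this is done. Variables may be dropped for extensive missingness or limited clinical relevance. No rule ties model size to the number of events.
- **Statistical analysis, propensity methods.** Matching or weighting on a propensity score is a sensitivity analysis that "may additionally be performed depending on event numbers and covariate balance".
- **Sample size.** "an average SSI incidence of approximately 17.5% was assumed for the standard treatment cohort", with a halving under irrigation, "corresponding to an expected SSI rate of 8.75% in the HOCl cohort"; "approximately 160 procedures (80 retrospective and 80 prospective cases) are anticipated during the predefined observation periods". The stated purpose is to estimate effect sizes and to supply data for sizing later randomised trials.

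**The concern.** Choosing covariates in advance and limiting their number solve different problems. The first stops the analyst from picking the model by its results. The second keeps the number of estimated coefficients in proportion to the number of infections. The article announces the second aim and carries out only the first.

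When a logistic model has few events per coefficient, maximum likelihood estimates tend to lie too far from the null, their variance grows, and sparse factor levels can produce coefficients that do not converge. The adjusted odds ratio is the study's main product and is meant to feed the sample size of a later trial. An odds ratio that is systematically too far from 1 would make that trial too small. If the model failed to fit, the analyst would have to shorten it after seeing the data, which the plan wants to avoid.

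**Working it through.** **1. Reproduce the plan's own figure.** Inputs from Sample size: 80 per cohort, 17.5% versus 8.75%, and the test ("Using a two-sided Fisher’s exact test with an α level of 0.05"). Summing the binomial probabilities of all outcome pairs for which Fisher's test gives p ≤ 0.05 yields a power of 29.89%. The article states an "estimated statistical power of approximately 29.9% for detecting the assumed effect size". The planning inputs are therefore read correctly.

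**2. Expected events.** 80 × 0.175 + 80 × 0.0875 = 14 + 7 = 21 (simulated 95% range about 13 to 30).

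**3. Parameters, intercept not counted.**
- Minimum, one term per covariate: 11 + 1 for exposure = 12.
- Categorical coding: exposure 1; age, sex, Charlson, alloplastic material, diabetes, BMI and duration 7; wound class 3 (four levels in Data collection); procedure type 3 (four examples in Data collection); ASA 3 and smoking 2 (assumed). Total 1 + 7 + 3 + 3 + 3 + 2 = 19. The article does not fix this coding.

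**4. Events per parameter.**

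| Control rate, HOCl rate | Events | ÷ 12 | ÷ 19 |
|---|---|---|---|
| 5%, 2.5% | 6 | 0.5 | 0.3 |
| 17.5%, 8.75% (plan) | 21 | 1.75 | 1.1 |
| 30%, 15% | 36 | 3.0 | 1.9 |
| 17.5%, 17.5% (no effect) | 28 | 2.3 | 1.5 |

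Across the article's 5–30% range with its 50% reduction, the ratio never exceeds 3. If one allows 5 to 10 events per parameter (an assumption, not in the article), 21 events carry 21/10 ≈ 2 to 21/5 ≈ 4 parameters, including exposure.

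**5. Effect on the estimate.** Simulation with 2,000 data sets of 160 procedures, calibrated to the planning rates. Assumptions not in the article: independent covariates, assumed prevalences including sparse upper wound classes, and covariate log odds ratios of 0.25 per SD (continuous) or 0.35 (binary or factor level).

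| Quantity | 12 parameters | 19 parameters |
|---|---|---|
| True log-OR (OR) | −0.826 (0.44) | −0.833 (0.43) |
| Mean ML log-OR (OR) | −0.992 (0.37) | −1.089 (0.34) |
| Inflation | 20% | 31% |
| SD, ML / unadjusted | 0.66 / 0.54 | 0.72 / 0.53 |
| 95% interval coverage, ML | 94.2% | 92.6% |
| Separation or non-convergence | 2.5% | 70% |
| Mean Firth log-OR (SD) | −0.840 (0.54) | −0.832 (0.56) |

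ML means, SDs and coverage use converged fits only. Inflation is the mean estimate divided by the true value, minus 1: 0.992/0.826 − 1 = 20%; 1.089/0.833 − 1 = 31%.

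A separate run with 12 terms gave a mean of −0.99 against a true −0.84, and −0.83 with Firth. A run with 15 terms gave −1.01 against −0.79 (27%), and −0.80 with Firth.

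**6. No true effect (about 28 events).** The mean log-OR was 0.003 with 12 parameters and 0.006 with 19, so there is no directional bias. The SD was 0.51 and 0.56, against 0.44 and 0.43 unadjusted. Coverage was 94.0% and 93.3%. Separation or non-convergence occurred in 0.5% and 52% of data sets.

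**The case against.** The strongest reply has several parts.

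*The text does not contradict itself.* Data collection lists many more candidates, such as COPD, immunosuppression, colonisation, previous groin surgery, Rutherford class and albumin, so 11 is a restriction of that pool and the article evidently means it as the limited set. This stands. A reader might infer that the two statements cannot both hold. The accurate reading is that the restriction is too weak for about 21 events.

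*The odds ratio will not be exaggerated in every case.* This also stands. Under no effect there is no drift in either direction. Even under the assumed effect, the 12-parameter shift (0.992 − 0.826 ≈ 0.17) is a quarter of the estimate's SD (0.17/0.66 ≈ 0.25).

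*Intervals are not shown to be too narrow, nor false positives to be common.* With 12 parameters, coverage is about 94–95% and type I error about 6%. A reader might infer otherwise from the skewed estimates, but the check does not bear it out.

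*Frequent separation is not established.* With 12 parameters it ran from 0.5% to 2.5%. The 70% needs both categorical coding and sparse levels, and the article fixes neither. Collapsing of levels is commonly left to a fuller plan.

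*Extreme odds ratios among significant results are mostly a matter of power.* The unadjusted Fisher comparison alone has a median crude odds ratio of 0.25 among significant results, against an assumed 0.452. That is selection at the disclosed 29.9% power, and a smaller model would not remove it.

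*The study is exploratory, with descriptive p-values.* This lowers the severity. It does not dispose of the point, because Sample size makes the effect estimate itself the deliverable.

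**Conclusion.** The concern holds in a limited form. The named model has 12 to about 19 parameters for about 21 expected events, and predefinition does not bring it down to a size those events can support. These counts follow from the article, apart from the upper figure of 19, which rests on assumed coding. If the 17.5% includes infections after the early window used for the primary endpoint (the article does not say), there will be fewer events and the ratio falls further.

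The expected damage is conditional on a real effect of the assumed size. It is roughly 20% inflation of the log odds ratio with 12 parameters, some 20–30% or more with categorical coding, and an SD about a fifth larger than unadjusted with 12 parameters (0.66/0.54 = 1.21). The exact sizes depend on the assumed covariate distributions; the direction was the same in every run. Separation becomes a practical problem only if sparse categories are entered separately.

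This should be fixed before the outcome analysis, but in an openly exploratory study it does not invalidate the design.

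**What to change.** 1. Keep multivariable logistic regression as the primary analysis, but fit it by Firth's penalised likelihood with profile-likelihood confidence intervals. In the simulations this removed almost all the bias, even with the full list.
2. Preferably, also name a short covariate list sized to about 21 events, and state in advance how sparse factor levels are collapsed.
3. Make the propensity-score-weighted analysis on the full covariate list a definite sensitivity analysis and delete event numbers as its condition. The exposure model is fitted to 80 versus 80 procedures, so the infection count does not limit fitting it, although the outcome comparison still rests on about 21 events. Promoting weighting to the primary analysis is a matter of choice, since it targets a marginal rather than a conditional odds ratio.

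The cost is some rewording and slightly more analysis work with standard software. A shorter list means somewhat less covariate adjustment in the primary model, which the weighted sensitivity analysis partly offsets. Study status says that data acquisition is ongoing and outcome analyses are still to be reported, so the change can still be made in advance.
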